## Abstract

**Background/Objectives**: The placement of central venous access devices, including peripherally inserted central catheters (PICCs) and PICC-PORTs, is a routine procedure in oncology care. Usually associated with limited physical pain, these procedures may nevertheless generate significant anxiety and negatively influence the overall procedural experience. Virtual reality (VR) has emerged as a non-pharmacological intervention capable of modulating attentional and emotional responses during medical procedures; however, evidence in adult oncology patients undergoing vascular access placement remains scarce. The aim of this study is to evaluate the effect of VR on an oncological patient’s overall procedural experience. **Methods**: This manuscript outlines the design and methodology of a prospective, single-centre randomised controlled trial. Adult oncology patients scheduled for PICC/PICC-PORT placement are randomised to receive standard care alone or standard care combined with an immersive VR intervention delivered via a head-mounted display during the procedure under pragmatic, real-world clinical conditions. The primary outcome is a composite patient-reported procedural experience endpoint, assessed through a non-aggregated framework encompassing procedural anxiety, comfort, satisfaction and procedural tolerability. Procedural anxiety constitutes the main quantitative driver; the remaining domains are analysed as individual component dimensions and interpreted jointly to contextualise the overall experience. Secondary outcomes include procedural pain, physiological parameters and procedural characteristics. A mixed-methods approach integrates quantitative assessment with qualitative phenomenological analysis. **Results**: The study is expected to provide methodological and clinical insight into the role of immersive VR in improving procedural experience and support future multicentre trials. **Conclusions**: This trial will contribute to the expanding field of digital and immersive health technologies by evaluating VR as a patient-centred adjunct intervention in oncological procedural care using a predefined patient-reported experience-based primary endpoint. The protocol has been submitted to ClinicalTrials.gov with the registration number NCT07384741.

## 1. Introduction

After recent advances in virtual reality (VR), this technology has been adopted in healthcare for a range of interventions, from clinical training and rehabilitation to mental health and pain management. VR systems offer an immersive and multisensory experience capable of capturing patients’ attention and potentially affecting their perception of medical procedures.

Recent studies have shown that, compared with conventional distraction techniques, VR has proven more successful in modulating pain and anxiety during clinical procedures by redirecting the patient’s focus towards engaging, calming environments and potentially influencing the neuromatrix of pain and anxiogenic input [1]. This process is thought to reduce the subject’s perception of discomfort and promote a state of relaxation and emotional containment [2,3,4]. Given that the side effects of virtual reality are generally mild, primarily including dizziness or nausea, often referred to as cybersickness [5,6], VR is considered a feasible and beneficial complement to standard care under local anaesthesia.

To date, the paediatric population has generated the most data supporting VR use in clinical settings [7], while adult patients undergoing invasive procedures are less studied. Nonetheless, recent studies in adult settings suggest that the use of VR may result in a reduction in procedural pain and anxiety without modifying or prolonging the duration of the procedure or increasing pharmacological sedation [3]. However, these studies are largely focused on the use of virtual reality in surgical settings; indeed, the recent meta-analysis by Lassen et al. [3] includes 37 articles, the majority of which were conducted in operative contexts, and only three investigate the use of VR during the insertion of central venous access devices (CVADs), which is the focus of the present protocol paper.

Oncology patients often require the placement of CVADs due to long-term intravenous treatments such as chemotherapy [8,9]. The placement of PICCs and PICC-PORTs is a minimally invasive procedure and does not result in immediate complications [10,11]; it is preferred because it avoids the use of peripheral venous access, which is unsuitable for most chemotherapeutic agents, reducing the risk of endothelial injury and extravasation of vesicant drugs, and allowing therapies to be delivered in outpatient or home-care settings [10]. However, despite these procedural and organisational advantages, patients may experience psychological distress associated with fear of the unknown, the emotional burden of a cancer diagnosis, and concerns about pain [12,13]. While procedural pain is usually described as mild and mainly related to the administration of local anaesthesia, anxiety levels appear variable and are strongly influenced by individual expectations and emotional vulnerability [14,15,16].

These observations indicate that CVAD insertion is not adequately described by pain intensity alone, but also by emotional and contextual components that play a role in the patient’s experience. This distinction is particularly crucial in oncological settings, where repeated and prolonged care pathways are common, and where patient experience and satisfaction can directly influence clinical outcomes and adherence to treatment [15].

As mentioned in the previous paragraphs, studies investigating the use of virtual reality during CVAD insertion are relatively limited: of the three randomised controlled trials included in the meta-analysis by Lassen et al. [3], two out of three use ports as the vascular access device [16,17], while only one focuses on PICC insertion [15]. These three studies confirm that the use of virtual reality appears to be a valid non-pharmacological strategy aimed at improving the overall procedural experience by reducing anxiety and pain scores without the need for increased analgesics or prolonged procedure times [16]. Virtual reality also appears to increase comfort, support a sense of emotional control, and enhance patient satisfaction and perceived quality of care [15,16,17], although only the study by Sargut et al. [16] reports statistically significant results.

Therefore, these studies conducted in the context of oncological CVAD placement support this broader clinical value in adult interventional procedures. Overall, while the aforementioned studies provide valuable preliminary evidence supporting feasibility and symptom modulation, they primarily focus on isolated symptom-based outcomes and do not evaluate procedural experience as a multidimensional patient-reported construct. In particular, no prior randomised controlled trial has been explicitly designed with patient-reported procedural experience as a predefined primary outcome in adult oncology patients undergoing PICC or PICC-PORT placement.

This study describes the design and methodology of a randomised controlled trial evaluating the effectiveness of an immersive VR intervention, delivered via a head-mounted display, during PICC and PICC-PORT placement in adult patients in an oncological setting.

### Outcomes and Aim

The primary outcome of this study is a composite patient-reported procedural experience endpoint, assessed immediately after the procedure. The primary analytical component of this composite endpoint is procedural anxiety, measured using a 10-point Visual Analogue Scale for Anxiety (VAS-A). The main statistical analysis will compare changes in VAS-A scores between the intervention group and the control group.

The additional dimensions of the composite endpoint, patient-reported comfort, satisfaction and procedural tolerability are collected concurrently and are not aggregated into a single score. These dimensions are analysed separately and interpreted jointly with procedural anxiety in order to provide an overall assessment of the patient’s procedural experience.

Secondary outcomes include: (1) procedural pain, assessed using a 10-point Visual Analogue Scale (VAS); (2) physiological parameters, including heart rate and arterial blood pressure; (3) procedural characteristics, such as procedure duration and number of device insertion attempts; (4) qualitative assessment of patients’ perceptions and lived experiences of the procedure, analysed using Van Kaam’s phenomenological method [18].

The aim of this study is to evaluate the effect of an immersive virtual reality intervention on the overall procedural experience of adult oncology patients undergoing PICC and PICC-PORT placement, with patient experience conceived as a primary dimension of quality of care.

## 2. Materials and Methods

### 2.1. Study Design

This study is designed as a prospective, interventional, randomised controlled trial (RCT) with a parallel-group design, conducted under real-world clinical conditions. The trial is conceived as an exploratory, pragmatic RCT aimed at evaluating the effectiveness of an immersive virtual reality (VR) intervention used as a non-pharmacological adjunct during PICC and PICC-PORT placement in adult oncology patients.

Participants are randomly allocated in a 1:1 ratio to one of two study arms: standard of care alone (SOC) or standard of care combined with immersive VR (VR + SOC). The study adopts a pragmatic approach, integrating the intervention into routine clinical practice without modifying standard procedural workflows and organisational conditions.

Due to the nature of the intervention, blinding of participants and healthcare professionals is not feasible. The trial is conducted at a single tertiary oncology centre and follows a superiority framework, with a composite patient-reported procedural experience endpoint as the primary outcome. This study protocol was developed in accordance with the Standard Protocol Items: Recommendations for Interventional Trials (SPIRIT) 2025 Statement [19].

The study is registered in ClinicalTrials.gov (ID: NCT07384741).

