### 2.7. Outcomes

The primary outcome of the study is a composite patient-reported procedural experience endpoint, reflecting the overall effectiveness of the virtual reality intervention during PICC and PICC-PORT placement. Although the term “composite endpoint” is used, it refers here to a conceptual and experiential framework rather than to a statistically aggregated outcome.

This composite endpoint integrates multiple dimensions of procedural experience, including:change in procedural anxiety, which represents the prespecified principal quantitative driver of the endpoint;patient-reported comfort and satisfaction with the procedure;perceived procedural acceptability and overall tolerability.

Procedural experience is assessed immediately after completion of the procedure (T1) using structured patient-reported measures, combining ordinal rating scales and qualitative evaluation to assess complementary quantitative and experiential elements. Procedural anxiety (measured using the 10-point Visual Analogue Scale for Anxiety, VAS-A) constitutes the primary focus of analysis, while the remaining component dimensions (comfort, satisfaction and procedural tolerability) are analysed as individual, non-aggregated measures and interpreted jointly with anxiety to provide an overall understanding of procedural experience. No numerical aggregation of component scores is applied.

This approach reflects the multidimensional and subjective nature of immersive digital interventions, for which patient experience constitutes a clinically meaningful outcome.

Secondary outcomes include:procedural pain, assessed using a 10-point Visual Analogue Scale (VAS);physiological parameters, including heart rate and systolic, diastolic and mean arterial pressure as routinely monitored;procedural characteristics, including procedure duration and number of insertion attempts;qualitative assessment of patients’ perceptions and lived experiences related to the procedure, analysed using Van Kaam’s phenomenological method [18].

This exploratory analysis aims to elucidate the relationship between procedural anxiety and the other experiential dimensions and to facilitate comparison with previous studies in which anxiety was evaluated as a standalone outcome. Procedural pain and anxiety are therefore analysed separately to explore their individual contributions to the overall procedural experience.

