### 2.10. Data Management Plan and Analysis

Study data will be entered into an electronic database in REDCap, used exclusively for data management and not for randomisation. All entered data will be pseudonymised, and access will be restricted to personnel specifically authorised for the study through dedicated password-protected accounts. The data will be stored on an institutional server of the study hospital and retained according to the relevant regulations. Identifiable information will be kept separate from research data, ensuring full confidentiality.

De-identified individual participant data, the data dictionary and the statistical code will be made available upon reasonable request to the Principal Investigator. No identifying information will be shared.

Given the minimal-risk nature of the study and its single-centre design, no formal monitoring of trial conduct is planned. The research team will oversee the study, protocol adherence and data collection as part of routine clinical practice.

All analyses will be conducted according to the intention-to-treat (ITT) principle. Descriptive statistics will be used to summarise participants’ demographic and clinical characteristics. Continuous variables will be reported as means and standard deviations or medians and interquartile ranges, as appropriate, according to variable distribution, while categorical variables will be presented as frequencies and percentages.

For the primary composite outcome, between-group comparisons will focus on procedural anxiety (VAS-A) as the prespecified principal quantitative driver of the composite endpoint. Independent samples Student’s *t*-tests, or non-parametric equivalents when appropriate, will be used for between-group analyses. Patient-reported comfort, satisfaction and procedural tolerability will be analysed as individual, non-aggregated component dimensions of the composite endpoint using appropriate parametric or non-parametric methods and interpreted jointly with anxiety. Secondary quantitative outcomes, including procedural pain and physiological parameters, will be analysed using similar inferential methods.

Within-group pre- and post-procedural comparisons will be explored using paired statistical tests. Statistical significance will be set at a two-sided *p* < 0.05.

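### The primary outcome is a four-domain composite with no success rule, although VAS-A is the named main analysis and the only basis of the sample size

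*Protocol article*

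**What the plan says.** Section 2.1 says that the trial "follows a superiority framework, with a composite patient-reported procedural experience endpoint as the primary outcome". Section 2.7 says of the term composite that "it refers here to a conceptual and experiential framework rather than to a statistically aggregated outcome", and adds: "No numerical aggregation of component scores is applied".

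The article does rank the domains. Outcomes and Aim states: "The main statistical analysis will compare changes in VAS-A scores between the intervention group and the control group". Section 2.10 says that "between-group comparisons will focus on procedural anxiety (VAS-A) as the prespecified principal quantitative driver of the composite endpoint", and bases the sample size on VAS-A alone.

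Comfort, satisfaction and tolerability nevertheless stay inside the primary outcome. Section 2.10 says that they "will be analysed as individual, non-aggregated component dimensions of the composite endpoint", to be read together with anxiety. None of the three appears in the list of secondary outcomes. Section 2.10 gives one significance threshold, two-sided 0.05, for the whole analysis.

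Two smaller points belong here. Section 2.7 describes the assessment of procedural experience, which is the primary outcome, as "combining ordinal rating scales and qualitative evaluation", and then lists qualitative assessment again among the secondary outcomes. Section 2.10 also plans within-arm tests: "Within-group pre- and post-procedural comparisons will be explored using paired statistical tests".

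**The concern.** A superiority claim needs one result, or a stated combination of results, that decides it. Here the claim is attached to something that has no score and no test of its own. The only instruction for combining the four domains is to interpret them together, which is not a decision rule.

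The difficult case is a null VAS-A comparison with a positive result on comfort, satisfaction or tolerability. All three are ratings by patients who know their allocation (section 2.5), and the sample size was not set for any of them. The Discussion makes a favourable reading of that pattern easy. It contrasts the chosen endpoint with symptom scores such as pain and anxiety, suggests that VR may do more for experience than for symptoms, and treats patients' awareness of the intervention as part of its effect.

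At stake is whether the final report can say unambiguously that the primary outcome was or was not met, and at what error rate.

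**Working it through.** **Inputs from the document (section 2.10 unless stated).** Difference 1.5 points on VAS-A; SD 2.5; two-sided alpha 0.05; power 80%; minimum 44 per group; target about 120, allocated 1:1 (section 2.1). Four domains in the primary outcome (section 2.7).

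**Assumption.** The article gives no correlations between the domains, so a common correlation r between the four test statistics is varied from 0 to 0.9.

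**1. The article's own figure.**
n per arm = 2 (z₀.₉₇₅ + z₀.₈₀)² (SD/difference)² = 2 × (1.960 + 0.842)² × (2.5/1.5)² = 2 × 7.849 × 2.778 = 43.6, so 44. This reproduces. The t-test version gives 44.6, a negligible difference. The calculation has one outcome and the full alpha of 0.05, so the trial was sized as if VAS-A were the single primary test.

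**2. Error rate if VAS-A alone decides.** One test at two-sided 0.05: 5%.

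**3. Error rate if any one of the four domains could carry the claim.** Under independence: 1 − 0.95⁴ = 1 − 0.8145 = 0.185. For correlated domains, four equicorrelated normal test statistics were simulated (1,000,000 draws) and the share with at least one |z| > 1.96 was counted. The last column counts only z > 1.96 in favour of VR, for which the single-test rate is 2.5%.

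| r | Any of four, two-sided | Any of four, favouring VR |
|---|---|---|
| 0 | 18.5% | 9.6% |
| 0.5 | 15.6% | 7.8% |
| 0.7 | 13.1% | 6.6% |
| 0.9 | 9.4% | 4.7% |

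**4. Effect of each remedy on the sample size.**
- VAS-A as the single deciding outcome: 44 per arm is unchanged. With an even split of 120, power at 60 per arm is Φ(1.5/(2.5 × √(2/60)) − 1.960) = Φ(3.286 − 1.960) = 0.908 (0.903 by the t-test).
- Bonferroni across all four domains: alpha is 0.05/4 = 0.0125, and n = 2 × (2.498 + 0.842)² × 2.778 = 62 per arm (64 by the t-test). Power for VAS-A at 60 per arm would then be about 77% to 78%.

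**The case against.** The strongest reply is that the article already sets a hierarchy. It names one main statistical analysis, describes VAS-A as the focus of the primary comparison, sizes the trial on it, and gives the other domains a contextual role in the Discussion. It also calls the trial exploratory, acknowledges expectation bias, and may leave multiplicity rules to an analysis plan that is not shown.

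Much of this stands. A reader might infer that the four domains are co-equal tests and that superiority may be declared on any one of them, giving an error rate of 18.5%. The document does not support that. It contains no any-of-four rule, the 0.05 threshold is stated globally rather than as a claim rule for each domain, and superiority on comfort with null anxiety would run against the stated ranking. Independence is also implausible for four ratings given by one patient within minutes of the procedure.

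Three further inferences should be resisted:
- The within-arm tests do not carry a superiority claim, since they are planned as exploratory. How often the two arms would disagree depends on the size of the pre-to-post fall, for which the article gives no figure.
- Acceptability cannot be said to lack an instrument. Section 2.7 pairs it with tolerability, which has a Likert scale in section 2.9.1, and the dataset in File S2 is not shown.
- The registry entry cannot be judged from here.

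The reply does not close the gap. No sentence says that anxiety alone decides superiority, and the three other domains remain part of the declared primary outcome. The exploratory label stands in section 2.1 beside a superiority framework. The definition of the primary outcome is the protocol's own task, so this is not a detail left to the analysis plan.

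**Conclusion.** The concern holds as an unresolved definition of the primary outcome. The main analysis is clear, but its authority over the superiority claim is not stated, so nothing prevents a positive result on an unblinded, unpowered domain from being reported as success on the primary outcome when anxiety is null.

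The size depends on which reading is adopted: 5% if VAS-A decides alone, and about 9% to 18.5% two-sided if any domain may carry the claim. The upper range rests on assumed correlations and on a reading that the article leaves open but does not adopt. The double listing of qualitative evaluation is a smaller inconsistency of the same kind. The matter should be settled before outcome data are analysed.

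**What to change.** State in Outcomes and Aim and in sections 2.1, 2.7 and 2.10 that the single primary outcome is the between-arm comparison of VAS-A, adjusted for T0 VAS-A, and that superiority is claimed on it alone at two-sided 0.05. With T0 as covariate, the estimated treatment effect is the same whether the T1 score or the change is analysed. Baseline VAS-A is already collected at T0. The sentence in section 2.10 that rules out formal adjustment would need an exception for this one covariate.

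Make comfort, satisfaction and tolerability secondary or supportive, reported either as estimates with 95% confidence intervals and no claim, or with Holm adjustment. List the qualitative data as secondary only. Report within-arm changes descriptively. Check the registry entry for consistency with the revised wording.

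The cost is a change of wording and, if the registry differs, an update there. The sample size stays as it is. The small downside is that superiority for overall experience can no longer be claimed on the strength of a secondary domain. If the four-domain primary outcome is to be kept, the alternative is an explicit success rule with alpha control; Bonferroni would need slightly more than 60 per arm to hold 80% power for VAS-A.

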### 2.2. Study Setting

The study is conducted at a research-focused oncology hospital in Northern Italy; it is a tertiary referral cancer centre within clinical areas routinely dedicated to the placement of central venous access devices. All procedures are performed according to institutional protocols for PICC and PICC-PORT insertion and under standard clinical conditions, ensuring that the intervention is fully integrated into routine care workflows without introducing additional burden for patients or staff.

Patient recruitment, intervention delivery, and data collection take place in real-world clinical settings, without modifications to standard procedural pathways, thereby enhancing the external validity and applicability of the study findings to everyday oncological practice.

